**Figure 3 F3:**
[figure not shown]
Physical exercise intervention protocol. Note: graph shows the time in minutes each participant spends at a specific intensity in percentage of their maximum heart rate.

### Video Game Intervention

For brain training video game intervention, Brain Age (Nintendo Co. Limited) has been used. To observe the proper results, we recommend the use of an active control group (Green and Bavelier, 2008). Tetris (Nintendo Co. Limited, Kyoto, Japan) has been shown as and has already been used as an appropriate active control to Brain Age (Nouchi et al., 2012, 2013) because it induces flow similarly to video games (Belchior et al., 2012), but it does not improve executive functions (Nouchi et al., 2013). Participants were instructed to play a commercial video game, either “Brain Age” or “Tetris,” for 15 min on a portable Nintendo Dual Screen (DS) × XL console. For Brain Age, the participants were required to play the Calculate × 100 and the Reading aloud games. Calculation × 100: the player must solve 100 simple arithmetic calculations as quickly as possible by writing the solution onto the touch screen of the Nintendo DS, Reading Aloud: participants read aloud excerpts from Japanese classical literature. Depending on the speed of the participants, they were asked to repeat from the beginning until finishing one run of the games. Tetris (Nintendo Co. Limited, Kyoto, Japan) is a 2D tile-matching puzzle video game. During the game geometric shapes composed of four blocks, each falling down one by one, and the player can move them to the side or rotate them while they are falling. The goal of the game is to keep the game going as long as possible. Therefore, the aim is to get a horizontal line of block with no gaps. The line disappears, providing more space and therefore more time. As the game progresses, the difficulty is increased by increasing the speed at which the geometric shapes fall down. The game ends when the player cannot manage to create full lines. Therefore, they can disappear, but the blocks pile up until the top of the screen. Tetris has been shown as and has already been used as an appropriate active control to Brain Age (Nouchi et al., 2012, 2013) because it does not improve executive functions. To familiarize the participants with the video games, they were practiced among the Stroop task at the first meeting and for 15 min in all after each session during a familiarization phase and before each session in the intervention phase.

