### Video Gaming

Video games elicit cognitive benefits (Granic et al., 2014), even in older adults (Zelinski and Reyes, 2009; Toril et al., 2014; Stanmore et al., 2017). Older adults are increasingly interested in playing video games (Zelinski and Reyes, 2009). They might have some potential for improving health-related issues, also in a clinical and rehabilitation framework (Primack et al., 2012; García-Betances et al., 2015). Nevertheless, the outcomes of video gaming for older adults are quite controversial. A meta-analysis from Toril et al. (2014) shows that cognitive functions of older adults benefit from video gaming in general, but it also revealed that executive functions do not reach significant levels. Other studies have revealed that the executive functions can be enhanced in older adults (Basak et al., 2008; Green et al., 2012; Strobach et al., 2012; Anguera et al., 2013). For a more detailed consideration please refer to the “Discussion” section. The usage of video games for acute interventions is on the rise, but many aspects remain to be answered (Guzmán and López-García, 2016; Monteiro-Junior et al., 2017). A salient question is: which game should be used for this purpose? First, it should have a beneficial effect on executive functions. Second, it should be conducted as an acute session to fit in the 20-min pause after the physical exercise. Third, the video game should be interesting also for older adults. One video game that fulfills all these requirements is Brain Age (Nintendo Co. Limited, Kyoto, Japan), also known as [name] Training. It is a popular brain training series based on the scientific work of [name] developed for handheld consoles from Nintendo (Kawashima et al., 2005; Uchida and Kawashima, 2008). It is meant to improve cognitive functions merely by playing a few minutes a day. Results demonstrated that common tasks among others such as simple arithmetic calculations and fast reading are beneficial for the executive functions (McDougall and House, 2012; Nouchi et al., 2012). Because Brain Age has only been conducted in a long-term setting with older adults (Nouchi et al., 2012), it is now to be examined whether it can also enhance the executive function in older adults in an acute intervention and whether there are additive effects if applied immediately after physical exercise.

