### Interventions Overview

To check whether the participants can perform moderate to vigorous exercise and as already conducted in other studies (Knowles et al., 2015; Hwang et al., 2016; Grace et al., 2018), the participants will attend the familiarization phase over the course of 1 week and three sessions in all. Training at the first session is only performed at moderate intensity. The duration at high intensity is increased gradually for the second and third session. At the end of each session, the participants also practice the Stroop task and the video games for a total of 15 min. In the following intervention phase, each participant will sequentially perform four interventions with one intervention per week (four interventions after 4 weeks in all). The interventions are conducted once a week because reports of earlier studies state that to achieve a sufficient recovery in older adults, a break of at least 5 days is necessary between high-intensity physical exercise sessions (Herbert et al., 2015). Every intervention consists of a warm-up for the Stroop task to prevent the learning effect (Green et al., 2014). Each is followed by the actual physical exercise at either high or low intensity. After physical training, the participants go to the next room, where they can sit down and directly start the video gaming session with either the brain training video game “Brain Age” or with “Tetris.” The intervention is finished by the fMRI session using the Stroop task to investigate its related brain activity. Because there are two variables with two levels each, the possible combinations sum up to a sequence of four different interventions that one participant must undergo in a Latin square counterbalanced order (see Figures 1, 2). Each week, all participants will perform interventions one after another from morning until evening on two consecutive days. Participants are instructed to avoid strenuous physical activity during the 48 h (Knowles et al., 2015) preceding each intervention session. Each participant is also asked to refrain from food for 1.5 h and to have only a light meal beforehand, to refrain from caffeine and alcohol for 24 h (Knowles et al., 2015) before each intervention. Participants are asked to maintain their current lifestyle and not to make any changes to their level of physical activity or diet (Coetsee and Terblanche, 2017b).

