As explained elsewhere (Klingberg, 2010; Green et al., 2014), to avoid learning effects, the Stroop task is practiced among the video games at the first meeting and for 10 min in all after each session during the familiarization phase and before each session in the intervention phase.

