### Expectation and Engagement

Apart from the degree of physical exercise, another issue is that improvements in cognitive functions also depend on psychological factors such as one’s expectation about the outcome (Boot et al., 2013a) or engagement during the intervention (Green et al., 2014; Benzing et al., 2016). This study is designed to address these issues by considering the expectations and engagement of the participants. At the first meeting, the study protocol is explained to participants, followed by a practice session with the Stroop task and both video games. They are told that it should be investigated whether high-intensity or low-intensity training and whether Brain Age or Tetris has a stronger effect on Stroop task and brain activity. The participants are blinded to the expected outcome and are asked after the last session of the familiarization phase and after the last session of the intervention phase about their subjective feeling to what extent the interventions might affect cognition (Boot et al., 2013a). Results of earlier studies suggest that differences of subject feelings (e.g., enjoyment, motivation, fatigue, satisfaction) between the experimental (high-intensity physical exercise, Brain Age video game) and control (low-intensity physical exercise, Tetris video game) condition might affect the improvement of cognitive function (Green and Bavelier, 2008). Because Brain Age and Tetris have been shown to have equal levels of engagement, it is expected that no significant difference exists in engagement between Brain and Tetris. In case there is a difference, it will be checked whether the performance at the Stroop task as well as the brain activity in the fMRI correlate with the engagement score. Based on the suggestion, the participants are asked to respond to questionnaires related to their subjective feelings weekly after each intervention (Boot et al., 2013a; Nouchi et al., 2013). Participants rated both questionnaires using a Likert scale, with 1 representing strong disagreement and 7 representing strong agreement with the given statements.

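### The article gives three conflicting accounts of practice before each intervention session, and two of them allow Brain Age to be played on Tetris (control) days before the outcome

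*Protocol article*

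**What the plan says.** The Protocol article describes pre-session practice in three places.

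- **Interventions Overview.** "Every intervention consists of a warm-up for the Stroop task to prevent the learning effect". Exercise follows, then one video game, then the Stroop task in the scanner. No game is mentioned before exercise, and the warm-up has no stated length. For the familiarisation sessions the same section says that "the participants also practice the Stroop task and the video games for a total of 15 min".
- **Video Game Intervention.** On what is practised, the section says: "To familiarize the participants with the video games, they were practiced among the Stroop task at the first meeting". Its wording for the length and the later occasions is: "for 15 min in all after each session during a familiarization phase and before each session in the intervention phase". The randomised exposure is separate: "Participants were instructed to play a commercial video game, either “Brain Age” or “Tetris,” for 15 min".
- **Cognitive Task.** The Stroop task is practised among the video games, starting from the first meeting. Here the length and the later occasions are given as: "for 10 min in all after each session during the familiarization phase and before each session in the intervention phase".

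Expectation and Engagement describes the first meeting as an explanation of the study "followed by a practice session with the Stroop task and both video games". Under Outcome, the primary measures are taken after each of the four interventions.

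**The concern.** The second primary hypothesis compares Stroop reaction time after Brain Age with that after Tetris. The third ranks the four exercise and game combinations. The sixth compares activation patterns between the two games. All three rely on Tetris days serving as a control for Brain Age. Video Game Intervention justifies Tetris on the ground that it leaves executive function unimproved, and that reasoning does not cover a control day that also contains Brain Age.

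If the pre-session practice includes both games, the comparison becomes more against less same-day Brain Age, where the design intends Brain Age against none. The Purpose section's aim of separating the contribution of each component would then be met less cleanly. The trial aims for 24 participants and states no power calculation, so there is no documented margin to absorb a weaker contrast.

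**Working it through.** **1. The three accounts side by side (intervention phase, before each session)**

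| Section | Tasks | Duration |
|---|---|---|
| Interventions Overview | Stroop warm-up only | not stated |
| Video Game Intervention | video games with Stroop | 15 min in all |
| Cognitive Task | Stroop among the video games | 10 min in all |

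The last two differ by 15 − 10 = 5 min for what reads as the same practice at the same time points. For the familiarisation phase, Interventions Overview agrees with the 15 min. One could take 15 min as the total and 10 min as the Stroop share, but both sentences describe an overall total and neither gives a split. That reading would in any case leave the conflict with the games-free warm-up.

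**2. Which games.** Video Game Intervention and Cognitive Task refer to the video games in the plural and do not restrict them to the day's assignment. The explicit statement that both games are practised is made only for the first meeting.

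**3. Brain Age minutes per session.** The Brain Age share of the practice, p, is not stated. Assume p = 2.5, 5 or 7.5 min.

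- Tetris day: p = 2.5 to 7.5 min, where the design intends 0.
- Brain Age day: 15 + p = 17.5 to 22.5 min, where the design intends 15.
- Difference: (15 + p) − p = 15 min whatever p is.

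**4. What that does to the contrast.** With a response linear in minutes, the difference of 15 min is intact and there is no attenuation. With an illustrative saturating response f(d) = 1 − exp(−d/k), the fraction of the contrast retained is

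[f(15 + p) − f(p)] / f(15) = exp(−p/k).

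| k (min, assumed) | p = 2.5 | p = 5 | p = 7.5 |
|---|---|---|---|
| 5 | 0.61 | 0.37 | 0.22 |
| 15 | 0.85 | 0.72 | 0.61 |
| 30 | 0.92 | 0.85 | 0.78 |

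This counts a minute played before exercise as fully as a minute played after it. Any fading in between reduces the attenuation.

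**5. Time from practice to scan.** Exercise lasts 38 min (high intensity) or 38 to 54 min (low intensity), followed by 15 min of the assigned game. The gap is therefore at least 38 + 15 = 53 min, and up to 54 + 15 = 69 min after the longest low-intensity session, before any changeover time.

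**6. Could the warm-up be a full Stroop run?** The article's session length reproduces: 192 × 2 + 96 × 2 + 72 × 4 + 24 × 6 = 1,008 s = 16.8 min. Neither 10 nor 15 min holds a full run.

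**The case against.** **The literal reading may not be what is done.** Each of the two sentences covers several occasions at once, and it is unclear whether the minutes, or both games, are meant to apply to the intervention phase. Interventions Overview has no games before exercise. The timeline figure is not shown and might settle the matter. This stands as a reason for caution about what happens in practice, but it does not remove the conflict in the text. The Dissemination Policy presents the article as the full protocol.

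**The exposure is shared and distant.** Practice precedes both game conditions alike and ends at least 53 min before the scan, and the game played directly after exercise still differs by the full 15 min. This stands: the practice gives Brain Age no advantage, and its effect may have faded by the scan.

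**A reader might infer near-complete dilution** from the Video Gaming section, which says of Brain Age: "It is meant to improve cognitive functions merely by playing a few minutes a day". The documents do not support that. The sentence describes the aim of a daily training product. The same section says that Brain Age has been studied in older adults only over the long term and that an acute effect is still to be examined. It supplies no single-session dose-response.

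**A reader might also infer that the plan discards a session baseline** by not modelling the pre-session Stroop task. The documents do not support that either. The reaction-time hypotheses compare conditions within participants, and a randomised crossover is valid without session baselines. Nothing says that the warm-up is recorded, and at 10 or 15 min it could not be a full run. Any precision gain depends on an unknown correlation ρ: the variance reduction is ρ², which is 1% at 0.1 and 25% at 0.5.

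**Conclusion.** The point holds as a contradiction between three sections with a possible consequence for the control condition. Followed literally, Video Game Intervention and Cognitive Task let the unassigned game be played before the outcome, so Tetris days need not be free of Brain Age, nor Brain Age days of Tetris.

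The consequence is possible attenuation of the Brain Age versus Tetris contrast. It is not a bias towards Brain Age. Its size cannot be determined from the documents: it is nil under a linear response and grows if the response saturates early. The 22% to 92% range rests on assumed practice shares, an assumed curve and no fading over the interval before the scan, so it is an illustration and not an estimate. The absence of a pre-session Stroop covariate is not an error in the plan.

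**What to change.** Reconcile Interventions Overview, Video Game Intervention and Cognitive Task so that all three state the same tasks and the same duration for practice before each intervention session. Limit that practice to the Stroop warm-up already described in Interventions Overview, or at least exclude the game not assigned that day. Leave game familiarisation to the first meeting and the familiarisation sessions.

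The cost is a change of text, with no added visit or procedure. The downside is slightly less game practice close to the session.

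If the Stroop warm-up is made a fixed, logged block, its result could enter a sensitivity analysis as a session-level covariate. This is optional, and the gain in precision is unknown.

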### Cognitive Task

The color-word matching Stroop task was adopted and conducted in an event-related design (Yanagisawa et al., 2010; Hyodo et al., 2012) using software (E-Prime 2.0.10.42, E-Studio 2.0.10.147; Psychology Software Tools, Inc., Sharpsburg, PA, USA). The participant is presented with two rows of words and is instructed to decide whether the meaning of the color word in white ink in the bottom row matches the color of the word in the first row. The participants can input their choice by pressing a button with the index finger and the middle finger to give “yes” or “no” responses. The order in which the participants must answer “yes” or “no” is randomized. The assignment, whether the index finger is “yes” and the middle finger is “no” or vice versa, is counterbalanced across participants and across the two halves of one experimental session. The correct answer rate assigned to yes and no is 50% each. The correct answer rate and reaction time are also measured.

Trials of two types are compared in the Stroop task. For the congruent trials, the top row were words “RED,” “BLUE,” “YELLOW” or “WHITE” printed in their respective ink and the bottom row contains the words “RED,” “BLUE,” “YELLOW” or “WHITE” in black ink. For the incongruent trials, the top row includes the words “RED,” “BLUE,” “YELLOW” or “WHITE” in an incongruent color, whereas the bottom row is the same such as in the congruent trials. Each experimental session consists of two halves separated by a small break, each with 48 congruent and 48 incongruent trials that are presented in random order. Consequently, the total number is 192 trials (96 congruent and 96 incongruent trials). All word stimuli are presented in Japanese. To prevent the participants from particularly addressing the bottom row and blurring out the top row, the top row is presented 300 ms earlier than the bottom row. Visual attention should shift automatically to the top row then (Zysset et al., 2007; Hyodo et al., 2012). The stimulus is presented on the screen for 2 s. To avoid prediction of the timing of the subsequent trial, each trial is separated by an interstimulus interval showing a fixation cross for 2 (96 trials), 4 (72 trials) or 6 s (24 trials). The whole session lasts around 16.8 min plus the brief pause between the two halves.

As explained elsewhere (Klingberg, 2010; Green et al., 2014), to avoid learning effects, the Stroop task is practiced among the video games at the first meeting and for 10 min in all after each session during the familiarization phase and before each session in the intervention phase.

### fMRI Session

All MRI data are acquired with a Philips 3-T scanner. In the scanner, stimuli are presented visually through a MRI-compatible monitor (BOLDscreen 32 LCD for fMRI; Cambridge Research Systems). Participants have a four-button fiber optic response box with their right hand, which is used to record behavioral responses. To examine the tasks specifically, participants wear earplugs to reduce the scanner noise. Head motion is minimized using foam pads and a headband. First, functional images are acquired using echo-planar functional images (EPIs) sensitive to blood oxygenation level-dependent (BOLD) contrast (64 × 64 matrix, TR = 2,000 ms, TE = 30 ms, flip angle = 70°, FOV = 24 cm, 34 slices, 3.75 mm slice thickness). Anatomical scans begin by acquiring a T1-weighted sagittal localizer series.

## Outcome

The primary outcome measures for all participants are the reaction time and correct answer count from the Stroop task as well as its related brain activity using fMRI after each of the four interventions. Additionally, the secondary outcome measures will be recorded similarly to the scores from the questionnaires for engagement after each intervention, the expectation after the familiarization phase and after the intervention phase, age, and gender at the first meeting.

### Randomization

We conduct four interventions per participant and use a Latin square counterbalancing that sums up to four sequences in all (see CONSORT flowchart). First, it would be wasteful for organizational purposes and costs for MRI to cover every possible sequence (24 in total) because it would necessitate 24 separate intervention sessions for each participant. Second, the risk of having a bias because of carry-over effects might be higher when two high-intensity bouts follow each other than with two low-intensity bouts because results demonstrated that biomarker for cognitive improvement (e.g., brain-derived neurotrophic factor, BDNF) might still influence the performance, even after 7 days (Skriver et al., 2014). It is not confirmed, but by separating the two high-intensity bouts from each other, it might decrease this bias. To make it more homogeneous, high-intensity and low-intensity bouts are conducted in an alternating fashion.

### Allocation and Implementation

Allocation of the participants to one of four sequences is done at the end of the familiarization phase (1 week before intervention phase) through a computer-generated sequence using random allocation software Graph Pad’s QuickCalcs Random Mumbers^1^. Based on a randomly assigned number list, the participants are allocated to each sequence.

### Blinding

Because of the study design, blinding is not properly possible because it is a non-pharmacological within-subject design. The intervention is visible to both, the participants as well as to experimenters who conduct the intervention. To somehow address this issue according to CONSORT, extension for non-pharmacological trials (Boutron et al., 2017), first, the participants are blinded to the study’s hypothesis. Second, we assess the expectation as well as the engagement and take them into consideration for the analysis.

